**2.3.6.5 Cognitive assessment**

**Task 1: Eriksen flanker task**

The Eriksen Flanker task will be used to assess selective attention and response inhibition.
^
15
^ Participants will be seated approximately 60 cm from a 24-inch monitor, with feet flat on the floor. A central target letter flanked by congruent or incongruent distractor letters will be presented for 1000 ms, followed by a 500 ms inter-stimulus interval. Participants will be instructed to respond to the central target letter while ignoring flanking stimuli, pressing ‘Q’ for target letters ‘H’ or ‘K’ and ‘P’ for target letters ‘S’ or ‘C’. A total of 96 trials (48 congruent, 48 incongruent) will be administered following 12 practice trials. Outcome measures will include mean reaction time (ms) and response accuracy (%) for congruent and incongruent conditions, and the flanker interference effect (incongruent minus congruent reaction time).

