**2.3.3 Inclusion criteria**
•Age 60–80 years, both sexes.•Clinical diagnosis of type 2 diabetes mellitus for the obese-diabetic group.•Body mass index (BMI) ≥ 25 kg/m
^2^ as per Asia-Pacific guidelines for obesity classification.
^
25
^
•Able to provide written informed consent independently or through a legally authorized representative.

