**2.3.4 Exclusion criteria**
•Presence of neurological or psychiatric conditions known to affect brain morphology or cognitive function (e.g., Parkinson’s disease, major depressive disorder, schizophrenia, prior stroke or traumatic brain injury).•History of neurodegenerative disease (e.g., Alzheimer’s disease, vascular dementia).•Type 1 diabetes mellitus or secondary forms of diabetes.•Active malignancy or any systemic illness likely to confound neuroimaging or cognitive assessments.•Contraindications to MRI (metallic implants, claustrophobia, cardiac pacemakers).•Current or recent (within 6 months) regular yoga practice (≥ 2 sessions per week).•Severe hearing or visual impairment precluding cognitive testing.

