**Task 2: N-Back memory task**

Working memory capacity and cognitive processing speed will be assessed using the N-Back paradigm.
^
31
^ Letter stimuli will be presented sequentially on screen at a rate of one per 2000 ms. Four conditions will be administered in sequence: 0-Back (respond when the letter ‘M’ appears), 1-Back, 2-Back, and 3-Back (respond when the current letter matches the letter presented 1, 2, or 3 positions previously, respectively). Each level will comprise 30 trials (10 targets, 20 lures/non-targets). Response accuracy (d-prime signal detection metric) and median reaction time will serve as the primary cognitive outcome measures for each N-Back level.

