**Step 3: Adaptation and manual preparation**

Selected practices will be adapted to accommodate the functional capacity of elderly obese-diabetic individuals. Modifications will include the use of props (chairs, bolsters, straps), reduced range-of-motion variants, seated and supine alternatives to standing postures, and graded progressions. A structured yoga manual will be produced, containing illustrated instructions, duration and frequency specifications, contraindication notices, and safety guidelines. The manual will be bilingual (English and Kannada) to ensure accessibility in the local population.

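### Both cognitive tasks use letter stimuli with no script criterion at entry, so scores may partly reflect familiarity with Latin letters, and the Phase 1 group comparison is not adjusted for education

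*Protocol article*

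**What the plan says.** **Stimuli.** In section 2.3.6.5 (Task 1), "A central target letter flanked by congruent or incongruent distractor letters will be presented for 1000 ms", with a further 500 ms between stimuli. Participants respond by "pressing ‘Q’ for target letters ‘H’ or ‘K’ and ‘P’ for target letters ‘S’ or ‘C", so four Latin letters map onto two Latin-labelled keys. Practice is short: "A total of 96 trials (48 congruent, 48 incongruent) will be administered following 12 practice trials". For Task 2, "Letter stimuli will be presented sequentially on screen at a rate of one per 2000 ms", and the lowest level is "0-Back (respond when the letter ‘M’ appears". M is the only N-Back letter named, so Latin script for that task is an inference, though a natural one.

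**Eligibility.** Section 2.3.3 lists age, diabetes status, BMI and consent ("Able to provide written informed consent independently or through a legally authorized representative"). It has no criterion on literacy, language or education. In section 2.3.4 the only exclusion worded around ability to do the cognitive tests is sensory: "Severe hearing or visual impairment precluding cognitive testing".

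**Language.** Section 2.4.2 (Step 3) says of the yoga manual: "The manual will be bilingual (English and Kannada) to ensure accessibility in the local population".

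**Analysis.** Section 2.3.6.7 compares the groups on cognitive outcomes by independent-samples t-test or Mann-Whitney U test. Years of education is a covariate only in the Phase 1 association regressions. It is not among the Phase 3 covariates named in section 2.5.10. Both tasks are secondary outcomes in both phases (sections 2.3.6.6 and 2.5.9), although cognitive function is part of the Phase 1 primary objective (section 2.3.1).

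**The concern.** The plan adapts its yoga material to a population that partly needs Kannada, but fixes letter stimuli for timed cognitive tests in people aged 60–80. Someone who seldom uses Latin letters may be slower or less accurate at telling H from K or S from C within a second, for reasons unrelated to attention or working memory. The affected scores are Flanker reaction time and accuracy, N-Back d-prime and N-Back reaction time.

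There are two consequences. Spread due to script familiarity makes a real group difference harder to see. And if familiarity differs between the obese-diabetic and obese-non-diabetic groups, for which no matching is described, the difference passes straight into an unadjusted comparison. The authors already treat education as a confounder in their association models, so leaving it out of the group comparison is inconsistent.

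**Working it through.** **Reading the sections together.** The Flanker stimuli and keys are Latin by statement, and the N-Back stimuli by inference from M. No entry criterion screens for familiarity with them. The plan foresees participants who need Kannada. The cognitive group comparison has no covariate related to literacy. All four premises are in the text or follow closely from it. The article does not give the number of people affected, so no stated figure is there to reproduce.

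**Illustration of size.** From the document: 40 per group, two-sided 5% level. Assumed: a share q of participants is unfamiliar with Latin letters, and they score D = 1 or 2 SD lower. The starting point is d = 0.634, for which 40 per group gives 80% power (noncentral t, 78 degrees of freedom).

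A share q shifted by D raises the within-group SD by the factor √(1 + q(1−q)D²). There are two models for the group effect:
- Model A: unfamiliar participants carry the same effect, so d_eff = d / √(1 + q(1−q)D²).
- Model B: they carry none, so d_eff = d(1−q) / √(1 + q(1−q)D²).

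Worked example, q = 0.10 and D = 1: the factor is √1.09 = 1.044. Model A gives 0.634/1.044 = 0.607; Model B gives 0.634 × 0.9/1.044 = 0.547.

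| q | D | d_eff A | Power A | d_eff B | Power B |
|---|---|---|---|---|---|
| 5% | 1 | 0.619 | 78% | 0.588 | 74% |
| 5% | 2 | 0.581 | 73% | 0.552 | 68% |
| 10% | 1 | 0.607 | 77% | 0.547 | 68% |
| 10% | 2 | 0.544 | 67% | 0.489 | 58% |
| 20% | 1 | 0.589 | 74% | 0.471 | 55% |
| 20% | 2 | 0.495 | 59% | 0.396 | 42% |
| 30% | 1 | 0.576 | 72% | 0.403 | 43% |
| 30% | 2 | 0.467 | 54% | 0.327 | 30% |

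**Imbalance with no true effect.** Let the share differ by Δq between groups around an average of 15%. The spurious standardized difference is about Δq·D / √(1 + 0.15 × 0.85 × D²). For Δq = 0.10 this is 0.10/1.062 = 0.094 (D = 1) or 0.20/1.229 = 0.163 (D = 2).

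| Δq | Spurious d (D = 1 to 2) | Rejection rate (nominal 5%) |
|---|---|---|
| 5 points | 0.047 to 0.081 | 5.5% to 6.5% |
| 10 points | 0.094 to 0.163 | 7% to 11% |
| 20 points | 0.188 to 0.326 | 13% to 30% |

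These figures treat the mixed scores as roughly normal. They apply to any one cognitive score for which the assumed shift is plausible. They show sensitivity and are not estimates.

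**The case against.** Neither task requires anyone to read English. The Flanker asks participants to sort four shapes onto two keys after practice, and the N-Back asks whether a shape recurs. A reader might infer that people not fluent in Latin letters cannot be validly scored. The documents do not support that: every participant yields reaction times, accuracy and d-prime, and the question is how purely these measure cognition. This part of the objection stands.

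The Kannada manual is also thin evidence. It contains prose instructions for yoga, and preferring Kannada for prose does not show inability to recognise single capitals. The plan expects participants to keep diaries and exchange text messages (section 2.5.7), which makes widespread illiteracy less likely. This stands as a limit on size. It does not remove the point, because nothing at entry checks letter familiarity.

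There are partial protections. The flanker interference effect and the Phase 3 changes are within-person differences, so a stable familiarity effect partly cancels. The Phase 1 association regressions already adjust for education. Mean reaction time, accuracy and d-prime are nevertheless outcomes in their own right, and the group tests have no such adjustment.

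A reader might also blame letter stimuli for apparent cognitive gain in Phase 3. Practice gain on a repeated task arises with any stimuli in a single-arm pre-post design, so changing the stimuli would not remove it.

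Finally, the full protocol may contain a language screen or a practice criterion that a condensed article omits. That is possible, so the absence of such rules is not the point here. The point rests on what the article fixes: the stimuli and the unadjusted test.

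**Conclusion.** The point holds in a limited form. The article fixes letter stimuli that depend to some degree on script familiarity, and pairs them with a group comparison that does not adjust for education. Familiarity can therefore enter the cognitive scores as noise, and can confound the Phase 1 contrast if literacy or education differs between groups.

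The size cannot be determined from the document. It depends on the assumed share, deficit and imbalance, and the power loss also depends on the model: at a 30% share it ranges from 72% down to 30%. With a small share and little imbalance the effect is slight. The primary vascular and imaging outcomes are untouched, and all participants remain scorable. The case for acting now is mainly that the change is cheap before testing starts, whereas the stimuli cannot be changed for baseline scores already collected.

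**What to change.** 1. **Flanker (section 2.3.6.5).** Before the first participant, replace the letters with left- and right-pointing arrows answered with left and right keys. Keep the 96 test and 12 practice trials, the timing and the outcome definitions, and use the same version at baseline and 6 months.
2. **N-Back.** Keep the letter version. Shapes or positions would move the task from verbal towards spatial working memory, a change of construct that this concern does not justify.
3. **Phase 1 analysis (section 2.3.6.7).** Compare the cognitive scores between groups in a linear model with group and years of education, instead of only by an unadjusted t-test or Mann-Whitney test. Education is already a covariate in the association regressions of that section, so no new variable is needed.

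**Cost.** One computer task is reprogrammed and two sections are reworded. The Data Availability statement says that no participant data had been collected at publication. Because the study is registered and ethics approval is reported, an amendment may be needed. Arrow results compare less directly with published letter versions, and the direct arrow-to-key mapping may change difficulty at the same timings. The education term costs one degree of freedom and adjusts for script familiarity only by proxy, so some confounding could remain in the N-Back scores.

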**Task 2: N-Back memory task**

Working memory capacity and cognitive processing speed will be assessed using the N-Back paradigm.
^
31
^ Letter stimuli will be presented sequentially on screen at a rate of one per 2000 ms. Four conditions will be administered in sequence: 0-Back (respond when the letter ‘M’ appears), 1-Back, 2-Back, and 3-Back (respond when the current letter matches the letter presented 1, 2, or 3 positions previously, respectively). Each level will comprise 30 trials (10 targets, 20 lures/non-targets). Response accuracy (d-prime signal detection metric) and median reaction time will serve as the primary cognitive outcome measures for each N-Back level.

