The mechanisms underlying brain alterations in obese-diabetic individuals are multifactorial, but vascular dysfunction plays a central and unifying role. Chronic hyperglycemia and dyslipidemia promote endothelial dysfunction, arterial stiffness, and impaired cerebrovascular autoregulation, collectively reducing cerebral perfusion and predisposing the brain to ischaemic injury.
^
9
^ Carotid artery intima-media thickness (cIMT), a validated surrogate marker of subclinical atherosclerosis, is significantly elevated in individuals with T2DM and is independently associated with reduced hippocampal volume and cognitive decline.
^
10
^ Furthermore, adipose tissue-derived proinflammatory cytokines, including interleukin-6 (IL-6) and tumor necrosis factor-alpha (TNF-α), disrupt the blood-brain barrier, foster neuroinflammation, and impair insulin signaling within the central nervous system, thereby compounding structural brain damage.
^
11
^ Insulin resistance in the brain has been specifically linked to tau hyperphosphorylation and amyloid-beta accumulation, suggesting a mechanistic overlap between T2DM and Alzheimer’s disease pathology.
^
12
^ Understanding these vascular-neural interactions is therefore critical to identifying therapeutic windows for intervention in elderly individuals with metabolic comorbidities.

Cognitive impairment is an important but frequently underrecognized complication of combined obesity and T2DM in the elderly. Longitudinal cohort studies indicate that individuals with both conditions face a substantially elevated risk of developing mild cognitive impairment (MCI) and dementia compared to those with either condition alone, suggesting additive or synergistic pathophysiology.
^
13
^ Domains most consistently affected include episodic memory, processing speed, executive function, and attentional control, all of which have significant implications for functional independence, quality of life, and adherence to self-management behaviors in this population.
^
14
^ Neuropsychological assessments such as the N-Back memory task and the Eriksen Flanker test provide sensitive and ecologically valid measures of working memory capacity and attentional inhibition, respectively, and have been employed in neuroimaging paradigms to establish structure-function relationships in metabolically at-risk cohorts.
^
15

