**Secondary outcomes**
•Eriksen Flanker task: mean reaction time and accuracy for congruent and incongruent conditions; flanker interference effect.•N-Back task: d-prime and median reaction time across 0-Back, 1-Back, 2-Back, and 3-Back conditions.

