**2.3.6.7 Statistical analysis**

All statistical analyses will be performed using Jamovi. Demographic and clinical characteristics will be summarised using descriptive statistics: mean ± standard deviation (SD) for normally distributed continuous variables; median and interquartile range (IQR) for skewed data; and frequencies with percentages for categorical variables. Normality will be assessed using the Shapiro-Wilk test. Group differences in neuroimaging and cognitive outcomes will be examined using independent-samples t-tests or Mann-Whitney U tests, as appropriate. A two-way ANOVA will be used to investigate interactions between group and sex or age; a nonparametric alternative (Kruskal-Walli’s test with Dunn’s post hoc correction) will be applied when distributional assumptions are violated. Associations between neuroimaging metrics, vascular parameters, metabolic indices, and cognitive performance will be explored using Pearson’s or Spearman’s correlation coefficients and multiple linear regression models, adjusting for age, sex, years of education, and physical activity level. A significance threshold of p < 0.05 (two-tailed) will be applied throughout.

### 2.4 Phase 2

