**Secondary outcomes**
•Change from baseline in the Eriksen Flanker task performance (reaction time and accuracy).•Change from baseline in N-Back task performance (d-prime and reaction time across all levels).

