**2.5.10 Statistical analysis**

Pre- and post-intervention neuroimaging and cognitive outcomes will be compared using paired samples t-tests (or Wilcoxon signed-rank tests for non-normally distributed data). Mixed-effects linear regression models will be used to examine the longitudinal trajectory of outcome variables, adjusting for relevant covariates (age, sex, baseline physical activity, HbA1c, and medication use). The association between intervention-induced changes in neuroimaging metrics and changes in vascular, metabolic, and cognitive outcomes will be examined using partial correlations and multivariate regression. Effect sizes (Cohen’s d and partial η
^2^) will be reported for all primary outcomes.

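### The N-Back is meant to measure both working memory and processing speed, but no load contrast against 0-Back is specified, so the per-level tests cannot tell the two apart

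*Protocol article*

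**What the plan says.** Section 2.3.6.5 (Task 2) of the protocol article opens: "Working memory capacity and cognitive processing speed will be assessed using the N-Back paradigm". The Introduction describes the N-Back and the Flanker as "sensitive and ecologically valid measures of working memory capacity and attentional inhibition, respectively", which for the N-Back names working memory alone.

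Four conditions are given: "0-Back (respond when the letter ‘M’ appears), 1-Back, 2-Back, and 3-Back". The first asks only for detection of a fixed letter. The task section makes d-prime and median reaction time (RT) outcomes at every level ("median reaction time will serve as the primary cognitive outcome measures for each N-Back level").

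The outcome lists repeat this and class the measures as secondary:
- Phase 1: "N-Back task: d-prime and median reaction time across 0-Back, 1-Back, 2-Back, and 3-Back conditions".
- Phase 3: "Change from baseline in N-Back task performance (d-prime and reaction time across all levels").

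The tests are "Group differences in neuroimaging and cognitive outcomes will be examined using independent-samples t-tests" (or the rank-based alternative) in Section 2.3.6.7, and "Pre- and post-intervention neuroimaging and cognitive outcomes will be compared using paired samples t-tests" (or the signed-rank alternative) in Section 2.5.10. The Phase 1 two-way ANOVA crosses group with sex or age. The Phase 3 mixed models list age, sex, baseline activity, HbA1c and medication as covariates. Load level is a factor in neither.

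**The concern.** A condition without memory load is normally included so that the loaded conditions can be compared with it. Here it is one more outcome in a row of four. The Flanker, in the same section, is treated differently: its interference effect (incongruent minus congruent RT) is defined and listed as an outcome.

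The gap matters in this population because the Introduction itself counts processing speed among the domains most consistently affected. A general RT difference between the groups is therefore expected in Phase 1, and it would appear at every N-Back level even if working memory were equal. In Phase 3 the same task is repeated after 6 months with no control group described, and a general retest speed-up would likewise appear at every level. What is at stake is which of the two stated constructs a result may be attributed to.

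**Working it through.** The plan gives no SD, correlation or expected shift for the N-Back, and its sample-size calculation is not tied to this task, so there is no figure of the plan's own to reproduce. The calculations below illustrate size under stated assumptions.

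**1. What each test estimates.** Write the group (or visit) difference in RT at level k as g + w(k), where g is common to all levels and w(k) is specific to load, with w(0) = 0.
- A test at level k estimates g + w(k).
- The 0-Back test estimates g.
- Only level k minus 0-Back, or equivalently the group-by-level term, estimates w(k).

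The plan specifies the first two and not the third.

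**2. Phase 1, general slowing only.** From the plan: 40 per group, two-sided 5%. Assumed: w(k) = 0, equal SDs, g = 0.3 or 0.5 SD. Noncentrality is g × √(n/2), with 78 degrees of freedom.
- g = 0.5: 0.5 × √20 = 2.24, rejection 60% at each level.
- g = 0.3: 0.3 × √20 = 1.34, rejection 26% at each level.

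Simulation (10,000 trials per case, between-level correlation 0.5 and 0.7):

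| Shift | Each of 1- to 3-Back | At least one of three | Each level minus 0-Back | At least one of three contrasts |
|---|---|---|---|---|
| 0.3 SD | about 26% | 43–48% | about 5% | about 13% |
| 0.5 SD | about 60% | 79–83% | about 5% | 12–13% |

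**3. Does showing 0-Back alongside solve it?** Only in part. In the same simulation, at least one of 1- to 3-Back is significant while 0-Back is not in 22–27% of trials at 0.5 SD and 21–27% at 0.3 SD. That pattern looks specific to memory although no load effect was built in.

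**4. Phase 3, general retest speed-up only.** The number of participants is not stated; 40 pairs is an assumption. With an assumed retest correlation of 0.7, the SD of change is √(2 × (1 − 0.7)) = 0.775. A speed-up of 0.3 baseline SD is then 0.3 / 0.775 = 0.387 SD of change. Noncentrality is 0.387 × √40 = 2.45, and each paired test rejects in 67%. Simulation with a between-level correlation of change of 0.5 gives at least one of three in about 89%. If 0.3 is instead taken in units of the SD of change, noncentrality is 0.3 × √40 = 1.90 and rejection is 46%. The contrast with 0-Back again rejects in about 5%.

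**5. How far the 5% can be trusted.** It follows from assuming equal SDs and an equal shift at every level, so it shows what the contrast does in that case and no more. Suppose the shift is equal in SD units (0.3 to 0.5), but the 2-Back SD is k = 1.5 to 2 times the 0-Back SD, with correlation 0.6. The raw contrast then has mean g(k − 1) and SD √(1 + k² − 1.2k).
- Smallest case (g = 0.3, k = 1.5): 0.15 / 1.204 = 0.125; rejection about 9% (40 per group) or 12% (40 pairs).
- Largest case (g = 0.5, k = 2): 0.5 / 1.612 = 0.310; rejection about 28% or 48%.

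A raw-scale contrast can therefore itself label scale differences or proportional slowing as a load effect. If slowing multiplies RT by a constant c, log(c × RT) = log c + log RT, so the shift is equal across levels on the log scale. The reverse also holds: a constant shift in milliseconds is unequal on the log scale. This is why both scales are needed.

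**The case against.** - **The attribution is not planned.** A reader might infer that the trial will report general slowing or speed-up as a working-memory effect. The article does not say so. It names processing speed as a second target and reports 0-Back beside the other levels, so a shift common to all four could be seen. This stands: the supportable wording is that a difference can be misread, not that it will be. Nor does any section plan to compare p-values between levels; step 3 shows only that doing so informally would be unsafe.
- **Mixed models are already planned.** Section 2.5.10 includes them for Phase 3, so it would be wrong to say the plan rests on t-tests alone. They carry no level term as described. An analysis plan that is not shown could add one. But the outcomes are written out in full at three places without a load contrast, while the Flanker contrast is written out, so this is more than brevity.
- **The argument is mainly about RT.** This stands. Slowing does not directly move d-prime, although lapses or inattention could lower it at all levels, and 0-Back d-prime may be at ceiling.
- **The contrast is not a cure.** This stands too (step 5). In Phase 3 a reader might infer that 0-Back replaces the missing control group. It does not, because practice gains larger at 2- or 3-Back would survive the subtraction.
- **The outcomes are secondary and all levels are collected.** True. This limits the weight of the point and also makes it cheap to settle.

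**Conclusion.** The point holds in this limited form. The plan claims two constructs for one task and states no test that separates them, although the reference condition is collected and the companion task has such a contrast. Per-level RT results at 1- to 3-Back are therefore ambiguous between a general shift and a load effect.

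The size depends on assumptions that the documents do not supply. The Phase 1 figure of about 60% per level needs a uniform shift of 0.5 SD with 40 per group, and falls to 26% at 0.3 SD. The Phase 3 figures also assume 40 pairs. These rates are not false-positive rates for the trial, because a speed difference is one of the things the task is meant to detect. They show how often a difference with no working-memory component would be significant at a loaded level. The point affects the interpretation of secondary outcomes and not the primary imaging and vascular results.

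**What to change.** Keep d-prime and median RT at each level as planned, and add one pre-specified load test per measure:

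1. **RT:** a mixed model with level (0 to 3) as a within-person factor, allowing variances to differ by level. The load test is the group-by-level term in Phase 1 and the visit-by-level term in Phase 3. The 0-Back contrast is the speed/attention reference.
2. **Scale:** fit RT in milliseconds and on the log scale, and claim a load effect only if both agree, so that proportional slowing is not taken for one.
3. **d-prime:** base the load test on the slope over 1- to 3-Back, because 0-Back may be at ceiling.
4. **Phase 3 wording:** state that, without a control group, practice gains that grow with load remain confounded with yoga, and that the contrast addresses only shifts common to all levels.

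Cost: wording in Sections 2.3.6.5, 2.3.6.7 and 2.5.10 and in the two outcome lists, plus one added test per measure and phase. No new data are needed. The downside is precision: the interaction is estimated less precisely than a single-level mean, so a null load test should be reported with its confidence interval and not read as showing that working memory is unaffected.
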